[figure not shown]

#### GENERAL INFORMATION ABOUT THE PROPOSED RESEARCH STUDY

##### 1. Study Title (Max. 255 characters including spaces)

Excess mortality during the COVID-19 pandemic

##### 2. Research Area (place 'X' in all boxes that apply)

|                          |   |                      |  |
|--------------------------|---|----------------------|--|
| Drug Safety              |   | Economics            |  |
| Drug Utilisation         |   | Pharmacoeconomics    |  |
| Drug Effectiveness       |   | Pharmacoepidemiology |  |
| Disease Epidemiology     | X | Methodological       |  |
| Health Services Delivery |   |                      |  |

### 8. Funding source for the study

Same as Sponsor?

Yes

Y

No

Institution/Organisation:

Address:

### 10. Data Access Arrangements

Indicate with an 'X' the method that will be used to access the data for this study:

Study-specific Dataset Agreement

Institutional Multi-study Licence

X

Institution Name

LSHTM

Institution Address

[name]

[figure not shown]

Will the dataset be extracted by CPRD?

|     |   |    |   |
|-----|---|----|---|
| Yes | X | No | X |
|-----|---|----|---|

If yes, provide the reference number:

We will extract data through the Define and Refine on-line tools. CPRD will extract the BMI, smoking and serum creatinine data from CPRD Aurum based on code lists that we provide (ref CPRD00050632)

#### INFORMATION ON DATA

#### 12. Primary care data (place 'X' in all boxes that apply)

|           |   |            |   |
|-----------|---|------------|---|
| CPRD GOLD | X | CPRD Aurum | X |
|-----------|---|------------|---|

Reference number (if applicable):

#### 13. Please select any linked data or data products being requested

**Patient Level Data** (place 'X' in all boxes that apply)

|                                               |   |                                                    |  |
|-----------------------------------------------|---|----------------------------------------------------|--|
| ONS Death Registration Data                   | X |                                                    |  |
| HES Admitted Patient Care                     | X |                                                    |  |
| HES Outpatient                                |   |                                                    |  |
| HES Accident and Emergency                    |   | NCRAS Cancer Registration Data                     |  |
| HES Diagnostic Imaging Dataset                |   | NCRAS Cancer Patient Experience Survey (CPES) data |  |
| HES PROMS (Patient Reported Outcomes Measure) |   | NCRAS Systemic Anti-Cancer Treatment (SACT) data   |  |
| CPRD Mother Baby Link                         |   | NCRAS National Radiotherapy Dataset (RTDS) data    |  |

[figure not shown]

|                               |  |                                                          |  |
|-------------------------------|--|----------------------------------------------------------|--|
| Pregnancy Register            |  | NCRAS Quality of Life Cancer Survivors Pilot (QOLP)      |  |
| Mental Health Data Set (MHDS) |  | NCRAS Quality of Life Colorectal Cancer Survivors (QOLC) |  |

**Area Level Data** (place 'X' in one Practice / Patient level box that may apply)

| Practice level (UK)                                                             |   | Patient level (England only)                        |   |
|---------------------------------------------------------------------------------|---|-----------------------------------------------------|---|
| Practice Level Index of Multiple Deprivation                                    |   | Patient Level Index of Multiple Deprivation         |   |
| Practice Level Index of Multiple Deprivation (index other than the most recent) |   | Patient Level Index of Multiple Deprivation Domains |   |
| Practice Level Index of Multiple Deprivation Domains                            |   | Patient Level Carstairs Index for 2011 Census       | X |
| Practice Level Carstairs Index for 2011 Census (Excluding Northern Ireland)     | X | Patient Level Townsend Score                        |   |
| 2011 Rural-Urban Classification at LSOA level                                   | X | 2011 Rural-Urban Classification at LSOA level       |   |

Reference / Protocol number (where applicable): 00053616

**14. Are you requesting linkage to a dataset not listed above?**

Yes ☐ No ☒

If yes, provide the Non-Standard Linkage reference number:

**15. Does any person named in this application already have access to any of these data in a patient identifiable form, or associated with an identifiable patient index?**

Yes ☐ No ☒

If yes, provide further details:

**VALIDATION/VERIFICATION**

**16. Does this protocol describe an observational study using purely CPRD data?**

Yes ☒ No ☐

**17. Does this protocol involve requesting any additional information from GPs, or contact with patients?**

Yes ☐ No ☒

If yes, provide the reference number:

[figure not shown]

## PART 2: PROTOCOL INFORMATION

| Applicants must complete all sections listed below
Applications with sections marked 'Not applicable' without justification will be returned as invalid |                                                                                                                                                                                                                                                                                                                                                                                                                                                                                                                                                                                                                                                                                                                                                                                                                                                                                                                                                                                                                                                                                                                                                                                                                                                                                                                                                                                                                                                                                                                                                                                                                                                                                                                                                                                                                                                                                                                                                                        |
|------------------------------------------------------------------------------------------------------------------------------------------------------------|------------------------------------------------------------------------------------------------------------------------------------------------------------------------------------------------------------------------------------------------------------------------------------------------------------------------------------------------------------------------------------------------------------------------------------------------------------------------------------------------------------------------------------------------------------------------------------------------------------------------------------------------------------------------------------------------------------------------------------------------------------------------------------------------------------------------------------------------------------------------------------------------------------------------------------------------------------------------------------------------------------------------------------------------------------------------------------------------------------------------------------------------------------------------------------------------------------------------------------------------------------------------------------------------------------------------------------------------------------------------------------------------------------------------------------------------------------------------------------------------------------------------------------------------------------------------------------------------------------------------------------------------------------------------------------------------------------------------------------------------------------------------------------------------------------------------------------------------------------------------------------------------------------------------------------------------------------------------|
| A. Study Title (Max. 255 characters, including spaces)                                                                                              | Excess mortality during the COVID-19 pandemic                                                                                                                                                                                                                                                                                                                                                                                                                                                                                                                                                                                                                                                                                                                                                                                                                                                                                                                                                                                                                                                                                                                                                                                                                                                                                                                                                                                                                                                                                                                                                                                                                                                                                                                                                                                                                                                                                                                          |
| B. Lay Summary (Max. 250 words)                                                                                                                     | 
Tracking of deaths in the population over time (mortality) is an essential part of monitoring and predicting the likely course of the COVID-19 pandemic. The number of deaths attributed to COVID-19 is problematic as likelihood of stating COVID-19 on the death certificate will have changed over time and may have been inconsistently applied across settings. Excess deaths by week from any cause could provide a more objective and comparable way of assessing the scale of the pandemic and formulating lessons to be learned. It is constructed by comparing the deaths over time since the start of the pandemic to the number expected based on the experience of previous non-pandemic years. Crucially this method has as the outcome all-cause mortality data, sidestepping the problems associated with attribution of cause of death to COVID-19.
 
Standalone national mortality data will allow tracking of excess mortality over time, but CPRD uniquely includes timely data on deaths alongside extensive clinical and demographic data, backed up by periodic linkages to national mortality data. This study will exploit this important combination of demographic/clinical and death data to examine how excess mortality during the course of the pandemic differs in individuals with different characteristics (e.g. age, sex, smoking) including pre-existing illnesses (e.g. respiratory disease, heart disease, diabetes). The study will provide key information to inform clinical guidance, resource planning and policies for protecting the most vulnerable.
                                                                                                                                                                                                                                                                                                                                          |
| C. Technical Summary (Max. 300 words)                                                                                                               | 
In recognition of limitations of cause-specific death data, estimates of excess mortality are routinely used to estimate and compare deaths due to seasonal influenza epidemics. These are based on national death registration data which allows for stratification by age, sex and geographic region. We aim to replicate these analyses for the COVID-19 pandemic in the UK with further stratification by COVID-19 effect modifiers that can be measured in primary care data.
 
Time series methods will be used in our primary analyses of observed mortality during the whole period (pre-COVID-19 and during COVID-19) using generalised linear models with a negative binomial error structure. The main outcome is mortality, measured in primary care data using the CPRD derived death date and the main exposure is the pandemic period (1st March 2020 onwards). The model will initially include exposure, age, sex, and terms to capture seasonality and underlying year-on-year trends. Interaction terms will be used to investigate excess mortality during the pandemic according to demographic, lifestyle-related and comorbidity characteristics. Relative and absolute differences in excess mortality will be described.
 
We will compare our primary time series approach to national excess mortality estimates. In a secondary analysis to check conclusions, we will compare weekly mortality with expected mortality based on comparable week-of-year mortality in the years prior to the pandemic (standardised mortality ratio (SMR) approach). We will also explore an approach based on individual-level cohort data, with the pandemic period included as a time-updated variable. In secondary analyses we will use updated linked ONS mortality data when available to repeat the analysis using the ONS death date and HES APC data to improve ascertainment of comorbidities.
 |
| D. Outcomes to be Measured                                                                                                                          | All-cause mortality                                                                                                                                                                                                                                                                                                                                                                                                                                                                                                                                                                                                                                                                                                                                                                                                                                                                                                                                                                                                                                                                                                                                                                                                                                                                                                                                                                                                                                                                                                                                                                                                                                                                                                                                                                                                                                                                                                                                                    |

[figure not shown]

## E. Objectives, Specific Aims and Rationale

### *Objective and aims:*

The overall objective is to inform public health policy by providing timely evidence on how key individual-level demographic characteristics and comorbidities affect excess mortality risk over time during the course of the COVID-19 pandemic.

### *Specific aims (primary):*

1. Validate approaches/data by estimating all cause excess mortality, by age, sex and co-morbidity grouping, over time by week, during the COVID-19 pandemic in the UK, and compare with similar estimates derived from national death registration data.
2. Use time series methods to investigate how all-cause excess mortality varies by key individual-level characteristics (demographics, lifestyle-related, comorbidities).

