## F. Study Background

Accurate and consistent estimation of key population parameters is required to inform national and global strategies to mitigate and suppress progression of the coronavirus disease 2019 (COVID-19) pandemic. Essential parameters include mortality due to COVID-19. However, variation in testing and recording of cause of deaths in national death registers between countries, over time and by underlying health conditions makes this challenging. Excess mortality over time may therefore be a more objective and comparable way of assessing the scale of the pandemic and formulating lessons to be learned. It is constructed by comparing the deaths over time in 2020 to the number expected based on the experience of previous non-pandemic years. Crucially this method has as the outcome all-cause mortality, sidestepping the problems associated with attribution of cause of death to COVID-19.

It is possible to estimate excess mortality by age, sex and geographic region using national death registration data although there is a delay in publishing these. These methods have been used to measure excess deaths in previous influenza seasons and are being used for the COVID-19 pandemic.

Current methods using death registration data alone do not allow stratified estimation of excess deaths for groups of people with clinical risk factors for COVID-19. CPRD uniquely includes timely data on deaths alongside extensive clinical and demographic data, backed up by periodic linkages to national mortality data. This study will exploit this important combination of demographic/clinical and death data to examine how pre-existing illnesses (e.g. respiratory disease, heart disease, diabetes) and risk factors such as BMI and smoking are associated with excess mortality risk during the course of the pandemic. The study will provide key information to inform clinical guidance, resource planning and policies for protecting the most vulnerable.

[figure not shown]

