### 1) Primary analysis - time series approach

We will derive weekly counts of numbers of deaths in contributing practices (see section L “Study Population”) from the start of the study period to the end of the study period. Population denominator sizes (number under active follow-up) will also be extracted. We will extract these counts overall, and stratified by age, sex, region and other factors (see section N “Covariates”). Where these factors are time-varying, counts will reflect changes over time.

We will fit generalised linear models with a negative binomial error structure to model the counts of deaths, taking account of variable denominator sizes [approach we took in Matthews et al media and statins paper to deal with variable denominators, BMJ2016]. The model will initially include the outcome (mortality), exposure (2020 pandemic period vs pre-pandemic), age, sex, interactions between the exposure and age and sex, Fourier terms (a harmonic function of calendar week) to capture seasonality, a continuous function of calendar year (linear, or higher order polynomial if evidence of non-linearity) to capture any underlying trends, and if relevant dummy indicators to capture extreme flu seasons. When investigating excess mortality within subgroups, further exposure covariate stratification factors will be added individually, and in combinations where there is sufficient information. Interactions between the exposure and stratification factors will provide estimates of the relative effect of the pandemic in strata.

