#### Validation of approaches / data

We will compare estimates of all cause excess age/sex-specific mortality over time by week during the course of the COVID-19 pandemic with similar estimates derived from national death registration data.

[figure not shown]

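### The planned validation against national data cannot check the comorbidity, smoking and BMI interactions that answer Aim 2, and the primary model names only a shared trend and season

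*Protocol*

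**What the plan says.** - **Section E, primary Aim 1:** validation consists of "estimating all cause excess mortality, by age, sex and co-morbidity grouping, over time by week", and the plan is then to "compare with similar estimates derived from national death registration data".
- **Section E, primary Aim 2:** time series methods will "investigate how all-cause excess mortality varies by key individual-level characteristics", covering demographics, lifestyle and comorbidities.
- **Section F:** national data can be split by age, sex and region, but "Current methods using death registration data alone do not allow stratified estimation of excess deaths for groups of people with clinical risk factors".
- **Section O, primary analysis:** a negative binomial model with Fourier terms and a continuous function of calendar year. The only interactions named are with the pandemic indicator: "Interactions between the exposure and stratification factors will provide estimates of the relative effect of the pandemic in strata".
- **Section O, validation paragraph:** "We will compare estimates of all cause excess age/sex-specific mortality over time by week". Comorbidity is not mentioned.
- **Other checks:** an SMR comparison using pooled pre-pandemic weeks, an exploratory cohort analysis, and the section J simulation. The closing section on changes to the protocol says that the SMR approach did not add anything and that the cohort analysis was not attempted.

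**The concern.** Aim 1 is meant to establish that the method works before Aim 2 relies on it. Agreement with national figures by age and sex shows that the expected deaths are right in each age/sex group. It does not show that they are divided correctly between people with and without, say, diabetes. An error in that division raises expected deaths in one stratum and lowers them in the other, so it almost cancels in any total that combines the two.

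The model leaves room for such an error. All strata share one trend and one season, and each characteristic gets its own term only in the pandemic window. A long-running difference in trend between people with and without the characteristic can therefore be absorbed by that term and read as a pandemic effect. The protocol intends these results to inform clinical guidance and the protection of vulnerable groups, so a passed national comparison could give unwarranted assurance about the study's main output.

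**Working it through.** **1. The plan's own figures (section J).** Pandemic IRR 1.89 (1.74-2.07) and comorbidity interaction 1.97 (1.85-2.08), both with true value 2.0. SE = ln(upper/lower)/(2 × 1.96) gives 0.044 and 0.030. The estimates lie -1.28 and -0.51 SE from 2.0, so both intervals cover the truth. The simulation cannot be regenerated because its settings are not given. As one reported run with a true interaction of 2.0, it does not show how often the model finds an interaction when there is none.

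**2. Sampling error.** Section I gives median weekly deaths in 2019 of 560 + 1,657 = 2,217. The first window, 1 March to 30 April 2020, is 61 days: 2,217 × 61/7 ≈ 19,320 deaths. If a characteristic accounts for a share p of deaths D, the SE of the log interaction is √[1/(Dp) + 1/(D(1-p))]. The shares are assumptions.

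| Share of deaths | SE | 95% limits around 1 |
|---|---|---|
| 30-50% | 0.016-0.014 | ×/÷ 1.03 |
| 10% | 0.024 | ×/÷ 1.05 |
| 5% | 0.033 | ×/÷ 1.07 |

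These are Poisson only. They use counts taken before overlapping practices are removed and before the continuous follow-up rule, so real intervals will be wider.

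**3. False interaction from a differing trend.** Let the log mortality rate in people with the characteristic change by g a year relative to the others. With a shared trend, the stratum main effect settles at the centre of the baseline and the interaction takes up the drift from there to the centre of the window: false interaction ≈ exp(g × distance). For 2020 the baseline centre is 1 March 2017 and the window centre is 31 March 2020, 3.08 years apart. Data truncated at a placebo window give distances of 2.58 (2019), 2.08 (2018) and 1.58 (2017) years.

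| g (assumed) | 2020 | Placebo 2019 | Placebo 2018 | Placebo 2017 |
|---|---|---|---|---|
| -1% a year | 0.970 | 0.974 | 0.979 | 0.984 |
| -2% a year | 0.940 | 0.950 | 0.959 | 0.969 |
| -3% a year | 0.912 | 0.925 | 0.939 | 0.954 |

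Fitting the model with shared terms to expected counts (2,217 deaths a week, share 25% or 30%, no pandemic effect) reproduces every entry to within 0.001. Overall observed/expected in the window is 1.00 throughout. Adding factor-by-year and factor-by-Fourier terms returns the interaction to 1.00.

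**4. How often it would look real.** Simulation with share 30%, 5% extra-Poisson variation per stratum-week and 150 runs per scenario. The 2020 interval excluded 1 in 3% of runs with no trend difference, and in 15%, 45% and 84% at -1, -2 and -3% a year. The 2019 placebo excluded 1 in 2%, 9%, 38% and 67%. With 150 runs the Monte Carlo error is up to about ±8 percentage points.

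**5. The SMR check.** Expected rates for a given week pool the same weeks of 2014 to 2019, on average (1+2+3+4+5+6)/6 = 3.5 years earlier. exp(3.5g) = 0.966, 0.932 and 0.900. The SMR ratio would agree with the false interaction, not expose it.

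**The case against.** - **A reader might infer that validation is against overall totals only.** It is weekly and specific to age and sex, so it can expose a false pandemic-by-age or pandemic-by-sex interaction. The gap concerns comorbidity, smoking and BMI.
- **A reader might infer that nothing with a known answer was tried.** The section J simulation has one, and recovers it. What is missing is a check where the true interaction is 1.
- **Differing seasons might be thought equally damaging.** That is not robust. With amplitudes of 0.20 and 0.12 (assumed), the false interaction runs from about 1.00 to 1.04 as the winter peak moves from the start to the end of January; 0.20 against 0.10 with an early-January peak gives 1.01. The SMR approach also gives each stratum its own weekly baseline. The case rests on trend.
- **The bias is small beside the interaction of 2.0 used in section J.** True. It matters for characteristics with weak modification, where 3 to 9% is comparable with or larger than sampling error.
- **A placebo value of 1 is only approximate, and one window has little power** (9% at -1% a year). Both stand: a severe flu season can truly affect some groups more. Section N lists 8 general covariates and 15 conditions, so three windows give at least 69 placebo estimates, of which about 3.5 would fall outside 95% limits by chance. A rule that changes the model after each exceedance would be unsound.
- **Placebo periods are a sensitivity analysis that could sit in a SAP.** Fair for that item alone. The mismatch between sections E, F and O and the shared baseline terms are in the protocol itself. Aim 1 could be read as comparing only what national data offer. That removes the contradiction but not the gap.

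**Conclusion.** The point holds in limited form. On the protocol's own account of national data, the planned validation cannot test the comorbidity, smoking or BMI interactions that answer Aim 2, and the stated model is open to a false interaction wherever mortality trends differ between strata. The size is about 3, 6 or 9% for trend differences of 1, 2 or 3% a year, with overall observed/expected near 1.00. These trend differences and the shares of deaths are assumptions, because the protocol gives neither. The sign follows the direction of the drift. The documents do not show that any reported interaction is wrong, and large interactions would be little affected. The change should be made because the study's main output otherwise has no check under a null, and one is available from six years of data already held.

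**What to change.** 1. **Sections E, F and O:** reconcile the three by limiting the national comparison in Aim 1 to the strata that registration data can provide, dropping comorbidity grouping from it.
2. **Section O, validation paragraph, add:** *The primary model, unchanged, will be fitted to data truncated at 30 April 2017, 2018 and 2019, with a placebo indicator from 1 March of that year, for each stratification factor. The three placebo interactions, expected to be about 1 apart from flu-season effects, will be shown beside the 2020 interaction and read together.*
3. **Section O, primary analysis, add:** *For every factor, a sensitivity model with factor-by-calendar-year and factor-by-Fourier terms will be reported beside the primary model, whatever the placebo results.* This one fixed response replaces ad hoc re-specification.

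Cost: three placebo fits and one sensitivity fit per factor, using existing code and data. The placebo fits have baselines of only three, four and five years, a single window has low power for a small bias, and intervals in the sensitivity model will be slightly wider.
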